# FAMily Motivational Engagement Strategy (FAMES) for coordinated specialty care programs: study protocol to evaluate a culturally responsive engagement intervention and equity focused implementation strategies in a hybrid type 2 randomized stepped-wedge trial

**DOI:** 10.1186/s13063-025-09280-0

**Published:** 2025-12-16

**Keywords:** Coordinated specialty care, Equity, Engagement, Family peers, Family members, Mental health services, Psychosis

## Abstract

**Background:**

Coordinated specialty care (CSC) models for first episode psychosis include evidence-informed family education and support as a core component of care. Evidence suggests low rates of family engagement in many CSC programs. To address this gap, the FAMily Motivational Engagement Strategy (FAMES), a culturally responsive intervention, was previously developed, pilot-tested, and found to positively impact family engagement in CSC. The goals of this Hybrid Type 2 Effectiveness-Implementation study are to investigate whether FAMES improves family engagement in CSC, assess activation of target mechanisms, and evaluate a Culturally Responsive Approach to Targeting Equity (CURATE) implementation package used to support the integration of FAMES in CSC.

**Methods:**

A stepped-wedge trial will be conducted with nine CSC sites, each randomized to one of three waves. CSC sites will initially recruit participant dyads into an attention control condition (*n* = 225) followed by a separate cohort of dyads who will receive FAMES (*n* = 225). Primary (engagement) and secondary (perceived stress, anxiety) outcomes, as well as mechanisms (self-efficacy, connectedness, motivation) among family members will be assessed. Secondary outcomes will also include client-level outcomes such as symptoms and engagement. Guided by the Reach, Effectiveness, Adoption, Implementation, Maintenance/Sustainability extension framework for sustainability, implementation outcomes (reach, adoption, implementation, sustainability) will be evaluated using mixed methods.

**Discussion:**

This study represents one of the first studies to test the effectiveness of a culturally responsive family engagement intervention in CSC settings, where service utilization disparities among families are present. Findings from this study have the potential to improve the impact of CSC for families and advance understanding of equity-focused implementation approaches to facilitate the provision of culturally responsive care in mental health settings.

**Trial registration:**

ClinicalTrials.gov NCT06945055. Registered on March 24, 2025. https://clinicaltrials.gov/study/NCT06945055.

**Supplementary Information:**

The online version contains supplementary material available at 10.1186/s13063-025-09280-0.

## Background

Each year approximately 150,000 individuals will experience their first episode of psychosis (FEP). If left untreated, psychosis can have detrimental impacts leading to poorer quality of life and increased mortality [1–3]. FEP is often considered a critical window for intervention to alter the short- and long-term outcomes associated with schizophrenia-spectrum illnesses and other psychotic disorders [4, 5]. Coordinated specialty care (CSC) models (e.g., NAVIGATE, OnTrack, and EASA) are early intervention programs for FEP in the U.S. [6]. Key components of CSC include evidence-based and evidence-informed practices, such as individual psychotherapy, education and employment support, peer support services, medication management, and case management for those in the early stages of psychosis, and family education and support (e.g., family psychoeducation) [7–12]. The inclusion of family education and support as a core component of CSC is primarily due to the added benefit that family member involvement in care has on client engagement, symptom reduction, and relapse prevention [13–15]. Over the past decade, robust literature has demonstrated the effectiveness and positive impact of CSC for individuals in the early stages of psychosis and their family members throughout the U.S. [6, 9, 13, 16–21].

### Impact of family member engagement and gaps in early psychosis care

Family members play a key role in providing support and resources for young people with FEP and are often instrumental in the initiation of mental health services for their loved one [22–25]. Despite a large proportion of young people with FEP reside with a family member coupled with the benefits of having family members engage in services (e.g., improved client engagement and clinical outcomes), many CSC programs in the USA struggle to reach family members, especially those from historically underserved or minoritized communities (e.g., rural, ethnoracial minorities) [22, 26]. Prior research has found that approximately 50% of client’s family members participate in family education and support appointments embedded with CSC [21, 27, 28]. In addition, families from ethnoracially minoritized and low socioeconomic backgrounds are significantly less likely than non-Latinx white and high socioeconomic families to be involved in CSC [27–29]. Lack of family engagement has been associated with client disengagement, lower functional outcomes, and could potentially reduce program fidelity [30–32]. Considering that existing literature has amplified a critical need to improve the reach of CSC and engagement in services among family members, there have been no large-scale studies on family engagement interventions for CSC in the USA. Moreover, no studies have addressed disparities in engagement in CSC or other early intervention services for psychosis.

### Blending of disparities research and implementation science to facilitate culturally responsive care

Culturally responsive care requires mental health services or programs to (1) use patient-centered approaches; (2) practice culturally competent care that is responsive to clients’ cultural perspectives and backgrounds, which is often facilitated by the use of cultural assessment tools; and (3) practice cultural humility, which is the ability to identify one’s own biases and the willingness to learn from others as well as enter into a relationship with clients with the intention of honoring clients’ beliefs, customs, and values [33–36]. The use of cultural assessment tools helps mental health providers to understand salient cultural and contextual factors [37, 38], and has been associated with improved communication, leading to stronger rapport, and overall satisfaction with mental health services [37, 39–41]. In addition, structural competency training provides the knowledge and skills to understand stressors and social determinants of health (e.g., stressors associated with poverty, food insecurity, racism/discrimination, stress associated with immigration) that can have an impact on mental health and engagement [42]. Eliciting salient cultural and contextual information can guide the tailoring of appointments or sessions, improve quality of care, and reduce disparities [43]. Yet, prior research suggests only 19% of CSC programs integrate formal cultural or structural assessments, and there has been no literature documenting implementation in CSC models [44]. This study protocol addresses this gap and could lead to advancements in the use of equity-focused implementation strategies to support the integration of culturally responsive interventions in CSC, and more broadly, mental health settings.

### Research objectives and aims

Informed by the Health Equity Implementation Framework which explicitly focuses on equitable implementation of interventions to address inequities in care [45], the overarching goal of this study is to improve family engagement in CSC and address disparities in engagement. To accomplish this, the present study has three aims: (1) to evaluate whether integrating FAMES improves family member/support person engagement in CSC compared to an attention control condition (ACC); (2) to examine whether target mechanisms of connectedness, self-efficacy, and motivation mediate FAMES engagement among family members/support persons; and (3) to assess the impact of FAMES on reach, adoption, implementation, and maintenance using a concurrent mixed-methods approach.

## Methods

### Study design

This Hybrid Type 2 Effectiveness-Implementation trial will use a cluster-randomized modified stepped-wedge design (see Fig. 1). Nine CSC sites throughout the USA, in both rural and urban regions, will be randomized to one of three start dates (waves) [46, 47]. Each site will recruit participant dyads, comprised of family member/support persons and clients with FEP enrolled in CSC, with separate cohorts of participant dyads recruited into the ACC and FAMES conditions. Aim 1 (effectiveness) seeks to evaluate whether integrating FAMES improves family engagement in CSC compared to ACC. In Aim 2 (mechanisms of change), we will use quantitative survey data to examine whether our theoretically driven target mechanisms of connectedness, self-efficacy, and motivation mediate FAMES engagement. Aim 3 (reach, adoption, implementation, and maintenance) will use a concurrent (quan + QUAL) mixed methods approach to evaluate implementation through an equity-focused lens. This study follows the Standard Protocol Items: Recommendations for Interventional Trials (SPIRIT) reporting guidelines (see Additional file 1 in the supplementary materials for the SPIRIT checklist) [48].

**Fig. 1 Fig1:**
[figure not shown]
Overview of Hybrid Type 2 Effectiveness-Implementation Study Design

### Study sites

Nine CSC programs geographically distributed throughout the USA will serve as study sites. The geographical location of sites represents both rural and urban communities, hospital-based and community-based programs, and has a combined ethnoracially diverse set of families. CSC programs are generally comprised of a program director, family education and support specialist, peer support specialist, case manager, education and employment specialist, and a medical prescriber. Nine part-time family peers, with lived experience of having a loved one who has experienced psychosis, will be hired by each CSC at least three months prior to the pre-implementation phase. Across the nine CSC sites, the following team roles will be consented to participate in study activities: Program directors/supervisors (*n* = 4), family education and support providers (*n* = 4), program director/family education and support provider (*n* = 4), and family peers (*n* = 9).

### Randomization

CSC programs will be randomized to one of three waves with different study start times offset by three months (Fig. 2). A two-stage stratified randomization procedure will be applied to account for differences in site size (large vs. small), using a median split by site panel size to designate sites as large or small. This block randomization method stratified by the size of the CSC program will ensure small and large sites have a balanced opportunity to receive the innovation at any point in the study timeline. To reduce the possibility of implementation contamination, study staff will perform each randomization incrementally at six months prior to the start date for the next wave.

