**Fig. 2 Fig2:**

The modified stepped-wedge randomized trial across three waves. CSC, Coordinated Specialty Care; ACC, Attention Control Condition; FAMES, Family Motivational Engagement Strategy; CFI, Cultural Formulation Interview

After site randomization, each CSC program will be allotted 18 months to recruit participant dyads to receive the ACC during the control phase, after which sites will participate in a three-month pre-implementation phase to commence training of family peers, program directors, and family education and support providers, followed by a 30-month active implementation phase to recruit a new cohort of participant dyads to receive FAMES (Fig. 2).

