**Other indicators (to be used as covariates/independent variables in analyses if Aims 1–2)**			
*Individual characteristics*	**Family member and client characteristics** will be assessed using modules from the *PhenX Toolkit Social Determinants of Health Core and social determinants of health*. Age, gender identity, sex, race, ethnicity, education, employment, marital status, religious preference, health insurance, etc	Family & client participant survey	BL
*Contextual factors*	**Contextual factors** will be assessed using the *Citizenship Measure* is a 46-item that measures community connectedness and engagement [70]	Family participant survey	BL
*Program characteristics*	**Program characteristics** will include setting, location, # of team members	Provider survey	BL

*BL *baseline, *PRE *pre-implementation phase, *FU *3-month post follow-up

Implementation outcomes are guided by the extension Reach, Effectiveness, Adoption, Implementation, Maintenance/Sustainability (RE-AIM) extension framework which identifies indicators related to sustainability and health equity-related considerations for tracking each domain of RE-AIM [71–74]. Table 2 outlines all measures to capture implementation outcomes which will be completed by family peers and CSC providers (i.e., family peers, program directors, and family education and support providers). Research staff will email participating CSC providers a unique REDCap link to complete pre- and post-training surveys during the pre-implementation phase. A longitudinal qualitative research approach will be used to explore potential barriers and facilitators to delivery and engagement that may inform modifications to implementation over time and understand experiences over time during the active implementation phase [77–79]. Semi-structured qualitative interviews will be scheduled and conducted via videoconference (i.e., Zoom) with family peers at baseline (end of pre-implementation phase) and at 6, 12, and 24 months after the commencement of the active implementation phase. Interviews will also be conducted with family education and support providers and/or program directors at baseline and at 12 and 24 months after the commencement of the active implementation phase. All interviews will be audio recorded, transcribed verbatim, and reviewed for accuracy.

**Table 2 Tab2:** Implementation outcomes: study assessments

Construct	Measure	Data source	Timepoint

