#### Aim 1: Impact of FAMES on primary and secondary outcomes

##### Quantitative data analysis

Statistical analyses for primary engagement outcomes will use Generalized Linear Mixed Models (GLMM) to compare engagement rates between the control (ACC) and intervention (FAMES), with a random effect for cluster (site), a fixed effect for each phase (ACC and FAMES), and a fixed effect for implementation wave to control potential time-related confounding [80, 81]. GLMM will also be used to assess change scores on secondary outcomes for family member and client participants from baseline to 3 months. Restricted maximum likelihood estimation with Kenward-Roger standard error and degrees of freedom correction to accommodate for our relatively small number of clusters will be used. Supplemental analyses will assess the likelihood of including relevant individual and program covariates (e.g., age, biological sex, race, and others) in models if significant differences among covariates occur between ACC and FAMES samples. Analysis of the secondary outcomes collected only from FAMES participants at follow-up will employ GLMMs to compare baseline to 3-month to follow-up inventory scores as a random effect repeated measures factor. Fixed effect covariates (e.g., age, biological sex, race, and others) will be included in these models as appropriate. A Bonferroni correction will be applied to primary engagement outcomes (first session attendance and total attendance per family and client) to control for multiple testing.

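### Randomisation is stratified by site size, but the stated Aim 1 model omits the stratum; adding it is nearly free and removes a small, conditional bias

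*Protocol article*

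**What the plan says.** The Randomization section makes site size the stratification factor ("A two-stage stratified randomization procedure will be applied to account for differences in site size (large vs. small"), formed by "using a median split by site panel size to designate sites as large or small". Study design states that "Nine CSC sites throughout the USA, in both rural and urban regions, will be randomized to one of three start dates (waves", and the Randomization section offsets the waves by three months. Every site supplies both conditions, "with separate cohorts of participant dyads recruited into the ACC and FAMES conditions". The text under Fig. 2 says that "each CSC program will be allotted 18 months to recruit participant dyads to receive the ACC during the control phase", followed by a three-month pre-implementation phase and 30 months in which the FAMES cohort is recruited. The totals are 225 ACC and 225 FAMES dyads; the article gives no quota per site.

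The Aim 1 quantitative analysis specifies a GLMM "with a random effect for cluster (site), a fixed effect for each phase (ACC and FAMES), and a fixed effect for implementation wave", the last term being there to control time-related confounding. Individual and program covariates may enter supplemental analyses if they differ significantly between the ACC and FAMES samples. The program characteristics in Table 1 "will include setting, location, # of team members". Number of team members is a proxy for size; panel size, which defines the strata, is not listed.

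**The concern.** The plan treats size as important enough to restrict the randomisation, then leaves it out of a model whose terms it spells out. A stratification factor is normally carried into the analysis unconditionally, and its inclusion should not hang on a significance test in a nine-site trial.

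The possible harm runs through accrual. ACC recruitment has 18 months and FAMES recruitment 30. A small site could fall short in the shorter window and catch up in the longer one, while a large site fills both. The ACC sample would then hold relatively more dyads from large sites than the FAMES sample does. A random site intercept with a small variance (the power section assumes an ICC of 0.01) absorbs site differences only in part, so some of any size effect could pass into the phase estimate.

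**Working it through.** **Inputs from the article:** 9 sites, 3 waves, 225 + 225 dyads (mean 25 + 25 per site), ICC 0.01, effect size 0.5, two-sided alpha 0.025, stated power above 85%.

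**Assumed, because the article does not give them:** three sites per wave; 5 large and 4 small sites (a median split of nine gives 4 and 5, and which stratum takes the median site is not stated); large sites per wave 2/2/1; a size effect γ of 0.2 to 0.4 SD; ACC enrolment by size; a linear scale.

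**1. The plan's own figure.** A stepped-wedge variance with 4 periods, 12.5 dyads per site-period, ICC 0.01 and period effects gives SE 0.1505. Power = Φ(0.5/0.1505 − 2.241) = 86.0%, consistent with the stated figure.

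**2. Bias formula.** For each site take the two cohort means, with V = diag(0.99/n_ACC, 0.99/n_FAMES) + τ² in every cell. X holds phase and wave, and z = 1 for a large site. If size is omitted, the bias in the phase effect is γ times the phase element of (X′V⁻¹X)⁻¹X′V⁻¹z.

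**3. Equal ratios.**
- 25/25 at every site: bias 0.000, including when one size is bunched in the early waves (large sites per wave 3/1/0). SE = √[0.99 × (1/225 + 1/225)] = 0.0938, with or without a size term.
- Large sites 40/40 and small sites 13/13: bias 0.000.

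**4. Ratios that differ by size.** FAMES is 25 at every site. The ACC splits keep the total: 5 × 33 + 4 × 15 = 225 and 5 × 37 + 4 × 10 = 225.

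An omitted size effect itself adds variance between sites, which the fitted intercept would pick up. Each wave has a 2:1 split of size, with sum of squares 2/3; three waves give 2 on 6 degrees of freedom, or 1/3. So τ² = 0.01 + γ²/3, which is 0.023 at γ = 0.2 and 0.063 at γ = 0.4.

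| ACC large/small | γ | Bias, τ² = 0.01 + γ²/3 | Bias, τ² held at 0.01 |
|---|---|---|---|
| 33/15 | 0.2 | −0.016 | −0.022 |
| 33/15 | 0.4 | −0.017 | −0.044 |
| 37/10 | 0.2 | −0.025 | −0.035 |
| 37/10 | 0.4 | −0.027 | −0.069 |

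The consistent column is 0.016/0.5 = 3% to 0.027/0.5 = 5% of the planned effect, against an SE of about 0.095.

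**5. Wider range.** With 4 large and 5 small sites, ACC/FAMES enrolment of 40/20 at large and 13/29 at small sites, and size effects from 0.1 to 1 SD, the bias is at most 0.035 SD with consistent τ². REML simulation (200 runs per case, many with convergence or boundary warnings) gave about −0.02 to −0.03 in the two stronger cases tried.

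**6. With the stratum in the model.** Bias is 0.000 in every scenario. At τ² = 0.01 the SE moves from 0.0944 to 0.0955 (33/15, +1%) and from 0.0953 to 0.0980 (37/10, +3%). In the calculation of step 1, power moves from 86.0% to 85.2%.

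**7. What wave means.** If the wave term stood for calendar period, with no term for the start group, large-site layouts 2/1/1 and 1/1/2 would give +0.19 and −0.19 per SD of size effect at ICC 0.01, even with equal accrual (0.04 to 0.08 SD for γ of 0.2 to 0.4). Adding either the start-group term or the size stratum brings this to 0.000.

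**The case against.** The strongest reply is that the design already handles most of this. Randomisation sets a start date and not a condition, each site serves as its own control, and the planned site and wave terms absorb most of any stable size difference. That stands, and it is why the bias is small. Nothing in the article shows that the ACC:FAMES ratio will differ by size or that size affects engagement; both are assumptions. The covariate provision is open-ended and could admit a size proxy, but it is supplemental and triggered by a test, so it does not replace a pre-specified term.

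Three stronger readings are tempting, and the article does not support them.

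- A reader might infer that because 4 and 5 sites cannot be spread evenly over three waves, size biases the FAMES contrast. With wave as the randomised group it does not: the bias is zero at equal ratios. At 35/25 (large) against 17/25 (small), the more lopsided layout 3/1/0 gives less bias than 2/1/1 (−0.037 against −0.108 per SD at τ² = 0.01), because the wave term absorbs size. Nor does the Randomization section promise equal counts; it speaks of a balanced opportunity for small and large sites.
- A reader might infer that it is enough for large sites to recruit more. The 40/40 and 13/13 case shows that it is not.
- A reader might take the τ² = 0.01 column as the size of the problem, which reaches 0.069/0.5 = 14% of the planned effect. That column pairs a planning ICC of 0.01 with a size effect that would itself raise the between-site variance. If the site variance were estimated as zero, which can happen with nine sites, the bias would be −0.032 to −0.064 (33/15) or −0.049 to −0.097 (37/10). That is a boundary case and not the expected result.

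**Conclusion.** The mismatch is real: size is the stratification factor, the stated Aim 1 model omits it, and the covariate provision is conditional and does not name it. Its consequence is minor. With wave as the randomised start group, bias requires both an enrolment ratio that differs by size and an effect of size on engagement. It is then about 0.02 to 0.03 SD, or 3% to 5% of the planned effect, under the assumed splits. The figures rest on assumed accrual, an assumed size effect, three sites per wave and a linear scale. The one reading under which the point would grow is wave as calendar period. The Randomization section uses wave for the start group, so the randomised-group reading is the natural one, but the model's stated purpose of controlling for time leaves room for doubt, and a definition would remove it.

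**What to change.** In all Aim 1 GLMMs, include the randomisation stratum (large/small, as fixed at randomisation) as a fixed effect, whatever any test of covariate differences shows. State in the same place that wave means the randomised start group. The stratum is already needed to randomise, so no new data are collected. The cost is a sentence or two in the analysis plan, one site-level degree of freedom, and an SE increase of about 1% to 3% in the unequal-accrual scenarios. Recruitment is expected to run to October 2029, so there is time to fix this before the final analysis. The balance statement in the Randomization section needs no change.
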